### 3. Risk parameters of metabolic diseases

#### 1) Anthropometric parameters

- Body weight and height are measured to the nearest 0.1 kg and 0.1 cm using an automatic scale after taking off the shoes and maintaining an upright posture (BSM370, BioSpace Inc., Korea).
- Waist circumference is measured at the midpoint between the lower rib margin and the iliac crest using a non-stretch clear measuring tape.
- Body mass index is calculated as weight (kg) divided by height squared ( $m^2$ )

#### 2) Body composition parameters

- Body fat and segmental lean mass (arms, legs and trunk) are measured by a bio-impedance analyzer after removing all accessories and metals (Inbody720, BioSpace Inc., Korea).
- Percentage body fat is calculated as body fat mass (kg) divided by weight (kg).
- Skeletal muscle mass is calculated from the sum of appendicular (arms + legs) and trunk lean masses (kg).

### 3) Blood gluco-lipid profiles

- Fasting glucose is analyzed using a hexokinase enzymatic method (Biosource, Nivelles, Belgium) with an assay reagent (Glucose HK Gen.3 kit, Germany)
- Fasting insulin is analyzed by an electrochemiluminescence immunoassay (Elecsys 2010, Roche, Indianapolis, IN, USA) with an assay reagent (Elecsys Insulin, Roche Diagnostic, Germany).
- Total cholesterol, triglycerides and high-density lipoprotein are analyzed using an enzymatic colorimetric method (Advia 1650, Siemens, Tarrytown, USA) with the Cholesterol and Triglycerides Liquiform (Labtest Diagnostica, Lagoa Santa, Brazil) and D-HDL kits (Siemens Diagnostics, Tarrytown, USA), respectively.
- The homeostasis model assessment (HOMA) indices are used to evaluate insulin resistance (HOMA-IR) and pancreatic  $\beta$ -cell function (HOMA- $\beta$ ). HOMA-IR is calculated as *fasting insulin* ( $\mu\text{U/ml}$ )  $\times$  *fasting glucose* ( $\text{mg/dl}$ ) / 405. HOMA- $\beta$  is calculated as  $360 \times \text{fasting insulin concentration}$  ( $\mu\text{U/ml}$ ) / [*fasting glucose* ( $\text{mg/dl}$ ) – 63]. Additionally, we confirm our findings using the HOMA2 approach. HOMA2-IR and HOMA2- $\beta$  data are calculated with a HOMA2 calculator released by the Diabetes Trials Unit, University of Oxford: HOMA Calculator. This calculator is available at: <http://www.dtu.ox.ac.uk/homacalculator/index.php>.

**Secondary outcomes** The serum levels of adipokines, inflammatory and cancer-related cytokines are measured as secondary outcome measures. After which, we will examine the relationship between the changes of each biomarker including cancer-related molecules elicited by an exercise program.

#### **Outcome measures**

##### 1. Serum levels of adipokines.

The serum concentration of leptin and adiponectin are measured by commercial ELISA kits (R&D systems).

- Leptin, minimal detectable density, 7.8 pg/ml; standard curve range, 15.6 - 1,000 ng/ml
- Adiponectin, minimal detectable density, 0.891 ng/ml; standard curve range, 3.9 - 250 ng/ml

##### 2. Serum levels of inflammatory-related cytokines

The serum concentration of IL-1 beta, IL-10, IL-11 and TNF-alpha are measured using commercial luminex multiplexed cytokine assay panels (R&D systems).

- IL-1 beta, minimal detectable density, 0.8 pg/ml; standard curve range, 17.8 - 4,320 pg/ml
- IL-10, minimal detectable density, 1.6 pg/ml; standard curve range, 13.7 - 3,340 pg/ml
- IL-11, minimal detectable density, 24.7 pg/ml; standard curve range, 0.5 - 125.4 ng/ml
- TNF-alpha, minimal detectable density, 1.2 pg/ml; standard curve range, 14 - 3,410 pg/ml

3. Serum levels of cancer-related molecules.

The serum concentrations of osteoprotegerin, osteopontin, and growth differentiation factor 15 (GDF-15) are measured by commercial luminex multiplexed cytokine assay panels (R&D systems).

- Osteoprotegerin, minimal detectable density, 3.62 pg/ml; standard curve range, 81.4 - 19,770 pg/ml
- Osteopontin, minimal detectable density, 413 pg/ml; standard curve range, 3.4 - 826.9 ng/ml
- GDF-15, minimal detectable density, 1.2 pg/ml; standard curve range, 34 - 8,270 pg/ml

4. Serum high-sensitivity C-reactive protein is measured by electrochemiluminescence immunoassay (Roche cobas 8000-e801, Roche Diagnostics, Tokyo, Japan).

### **Sample size**

No prior studies have investigated the minimal clinically important difference or change in the circulating levels of WISP-1 and the  $\beta$ -catenin focusing on breast cancer patients. However, according to a previous study focusing on patients with gestational diabetes mellitus, their serum WISP-1 levels were significantly higher by 20% compared to that of healthy pregnant women. In addition, according to another calorie restriction study focusing on obese patients, the rate of clinically meaningful reduction in circulating WISP-1 level was around 27.5% in obese women. Based on results from prior studies, a 25%-point difference in the serum Wnt signaling molecule levels within each group are considered to be significant in this study. In order to detect the rate of change between baseline and 12-week intervention in both groups, and to obtain a type 1 error rate of 5% and a power of 90%, a sample size of 17 subjects per study arm are needed. To account for an expected dropout rate of ~30%, we decided to increase this number to a group size of 25. Thus, a total of 50 breast cancer survivors will be included in the study. The minimum number of subjects for adequate study power was calculated with a sample size calculator released by ClinCalc LLC. This calculator is available at <https://clincalc.com/stats/samplesize.aspx>. The formula used for power and sample size calculations is as follows:

The anticipated mean and standard deviation of group #1 =  $2104 \pm 472$  pg/mL

The anticipated percent difference in outcomes of group #2 compared to group #1 = 25%

$$k = n_2 / n_1 = 1$$

$$n_1 = (\sigma_1^2 + \sigma_2^2 / K) \times (z_{1-\alpha/2} + z_{1-\beta})^2 / \Delta^2$$

$$n_1 = (472^2 + 472^2 / 1) \times (1.96 + 1.28)^2 / 526^2$$

$$n_1 = 17$$

$$n_2 = K \times n_1 = 17$$

$$\Delta = |\mu_2 - \mu_1| = \text{absolute difference between two means}$$

$$\sigma_1, \sigma_2 = \text{variance of mean \#1 and \#2}$$

$$n_1 = \text{sample size for group \#1}$$

[figure not shown]

$n_2$  = sample size for group #2

$\alpha$  = probability of type I error (set as 0.05)

$1 - \beta$  = probability of type II error (set as 90%)

$z$  = critical Z value for a given  $\alpha$  or  $\beta$

$k$  = ratio of sample size for group #2 to group #1

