### **Data analysis**

Feasibility measures (acceptability, adherence, and adverse events etc.) are reported as numbers and percentages. Reasons for declining participation are analyzed descriptively with numbers and percentages of subjects declining for various reasons. Descriptive statistics are calculated to identify the means and standard deviations (SD) or standard errors of the mean (SEM). After Shapiro-Wilk normality test and variances analysis, parametric paired t-test or non-parametric Wilcoxon signed-rank test are used to compare the levels of health-related fitness, body composition, and serum biomarkers between before and after training, as appropriate. Pearson's and partial correlations are calculated to assess the relationships between serum levels of Wnt signaling molecules and other clinical parameters. All data are analyzed using SPSS 22.0 software (SPSS, Inc., Chicago, IL, USA). All statistical tests are two-sided and  $P$ -values less than 0.05 are considered significant.

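### The 90% power with 17 per arm is claimed for a within-group change but computed for a between-group WISP-1 difference, so it fits neither the stated target nor the planned paired test, and β-catenin has no inputs

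*Protocol*

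**What the plan says.** Three parts of the protocol bear on the point.

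- **Target.** The Sample size section says that a "25%-point difference in the serum Wnt signaling molecule levels within each group are considered to be significant in this study". It introduces the calculation with "In order to detect the rate of change between baseline and 12-week intervention in both groups" and concludes that, for "a type 1 error rate of 5% and a power of 90%, a sample size of 17 subjects per study arm are needed". The sample-size row of the Study Protocol Summary says the same.
- **Formula.** The same section then prints the formula for two independent means. Its effect is given as "The anticipated percent difference in outcomes of group #2 compared to group #1 = 25"%, and Δ is defined as the "absolute difference between two means". "The anticipated mean and standard deviation of group #1" are 2104 and 472 pg/mL, and the SD of 472 is entered for both groups. The section does not label these figures as WISP-1. They carry the same citation as the 27.5% WISP-1 reduction mentioned just above them, a study of WISP-1 in obesity.
- **Test.** The Data analysis section, and the matching summary row, compare fitness, body composition and serum biomarkers before and after training by "parametric paired t-test or non-parametric Wilcoxon signed-rank test". No between-arm test is named. "All statistical tests are two-sided and" use a 0.05 threshold.

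The Objectives make the changes in both WISP-1 and β-catenin the primary aim.

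**The concern.** The text describes a change within persons, the formula describes a difference between two independent groups, and the planned test is the within-person one again. A paired calculation needs the SD of the change, or the pre-post correlation from which to derive it. The protocol gives neither. The two-group formula needs a between-arm test, and the protocol names none.

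The claim is also worded for Wnt signaling molecules in general, while every input comes from WISP-1. β-catenin has no mean, SD or expected effect.

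This paragraph is the only justification for randomizing 50 participants. As it stands, a reader cannot tell whether the 90% supports a conclusion about change inside an arm or about exercise versus control, and the second is the question a 1:1 randomized design exists to answer.

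**Working it through.** **Inputs from the protocol.** Mean 2104 and SD 472 pg/mL; Δ = 0.25 × 2104 = 526 pg/mL; two-sided α = 0.05; power 90%; allocation 1:1; dropout about 30%.

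**Input not in the protocol.** The pre-post correlation ρ. I assume a range of 0 to 0.7, with an SD of 472 at both visits.

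**Step 1: reproduce the stated figure.**
n = (472² + 472²) × (1.96 + 1.28)² / 526² = 445,568 × 10.4976 / 276,676 = 16.91, rounded up to 17.
The normal-approximation power at 17 is 90.1%. Allowing for dropout, 17 / 0.70 = 24.3, rounded up to 25. The arithmetic is right for two independent groups compared at one time point.

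**Step 2: the same contrast by exact t-test.**
Noncentrality = 526 / (472 × √(2/17)) = 3.25 on 32 degrees of freedom. Power is 88.3% with 17 per arm and 90.1% with 18.

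**Step 3: the planned paired t-test, 17 pairs.**
SD of change = 472 × √(2(1 − ρ)). Noncentrality = 526 × √17 / SD of change, on 16 degrees of freedom.

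**Step 4: a between-arm t-test of change scores, 17 per arm.**
Noncentrality = 526 / (SD of change × √(2/17)), on 32 degrees of freedom.

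| Assumed ρ | SD of change (pg/mL) | Paired test: power at 17 | Paired test: n for 90% | Change scores between arms: power at 17 per arm |
|---|---|---|---|---|
| 0 | 667.5 | 86.2% | 19 | 60.6% |
| 0.3 | 558.5 | 95.4% | 14 | 75.9% |
| 0.5 | 472.0 | 99.0% | 11 | 88.3% |
| 0.7 | 365.6 | over 99.9% | 8 | 98.2% |

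The paired test has exactly 90% power with 17 pairs only at ρ of about 0.12.

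**Step 5: week-12 levels between arms, adjusted for baseline.**
The residual SD is approximately 472 × √(1 − ρ²): 450 pg/mL at ρ = 0.3 and 409 at ρ = 0.5. With 17 per arm, power is about 91% and 95% respectively, against 88.3% at ρ = 0.

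**Step 6: β-catenin.**
No power can be computed from the protocol. As an illustration, take a 25% between-arm difference, 17 per arm and the normal approximation. Power is 90.1% if the coefficient of variation equals that of the WISP-1 inputs (472 / 2104 = 0.224), 68.1% at an assumed 0.3, 44.5% at 0.4 and 30.8% at 0.5.

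**The case against.** The best defence is that nothing is miscalculated and nothing need change in conduct. The printed formula gives 17. It suits a between-arm comparison of week-12 levels, a natural comparison for this design. For the paired test the protocol does plan, 17 pairs give at least 90% power for WISP-1 whenever ρ exceeds about 0.12. The gap between 88.3% and 90% is one participant per arm, the usual difference between a normal and a t calculation. A between-arm test may also be named in a statistical analysis plan that is not at hand.

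Most of this stands, and it limits what may be concluded. A reader might infer three stronger points, none of which the protocol supports:

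- **That the trial is underpowered.** For the paired test, the mismatch alone does not show it. A shortfall for change scores between arms depends on ρ being below about 0.5, and ρ is not given.
- **That both arms are expected to change by 25%, making the between-arm difference zero.** The text sets 25% as the change that counts as meaningful. It does not predict such a change in controls.
- **That power drops because two biomarkers share the 5%.** The protocol specifies no split of α.

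What the defence does not remove is the contradiction inside the Sample size section, and between it and the Data analysis section. A separate analysis plan could add a between-arm test, but the protocol would still claim its power for a within-group change, and for a marker with no inputs.

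**Conclusion.** The point holds as a mismatch of target, formula and test. The 90% was calculated for a between-arm difference in single-time-point WISP-1. It is stated for a within-group change in Wnt markers generally, and the named analysis is paired.

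Depending on which comparison is meant, power with 17 per arm runs from 61% (change scores between arms, ρ = 0) to over 99.9% (paired test, ρ = 0.7). It is 88.3% for the comparison the formula describes. These figures rest on the protocol's SD of 472 pg/mL, taken from the cited obesity study, on that SD applying at both visits, and on the assumed range of ρ. For β-catenin the claim has no basis in the document.

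The paragraph is wrong as written and should be restated. The finding gives no ground for a larger trial, and it is not evidence that the paired test lacks power.

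**What to change.** 1. In the Sample size section and the sample-size row of the summary, delete the phrases *within each group* and *in both groups*. State instead:

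> With 17 evaluable participants per arm (25 randomized, about 30% dropout), a two-sample t-test at two-sided 5% has about 88% power for a between-arm difference of 526 pg/mL (25% of 2104) in week-12 WISP-1, assuming an SD of 472 pg/mL. Adjustment for baseline raises this to about 91% if the pre-post correlation is 0.3 and 95% if it is 0.5. No power is claimed for β-catenin.

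2. In the Data analysis section and the statistical-analysis row of the summary, name the matching between-arm comparison of week-12 WISP-1 as the primary test, for example ANCOVA adjusted for baseline. Keep the paired tests as descriptive within-arm analyses. Without this second change, the new power statement would still describe a test the protocol does not plan.

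The cost is a slightly less favourable stated power and one added analysis. The sample size is unchanged.

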### **Data analysis**

Feasibility measures (acceptability, adherence, and adverse events etc.) are reported as numbers and percentages. Reasons for declining participation are analyzed descriptively with numbers and percentages of subjects declining for various reasons. Descriptive statistics are calculated to identify the means and standard deviations (SD) or standard errors of the mean (SEM). After Shapiro-Wilk normality test and variances analysis, parametric paired t-test or non-parametric Wilcoxon signed-rank test are used to compare the levels of health-related fitness, body composition, and serum biomarkers between before and after training, as appropriate. Pearson's and partial correlations are calculated to assess the relationships between serum levels of Wnt signaling molecules and other clinical parameters. All data are analyzed using SPSS 22.0 software (SPSS, Inc., Chicago, IL, USA). All statistical tests are two-sided and  $P$ -values less than 0.05 are considered significant.

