| Number of participants / sample size | 
A 25%-point difference in serum Wnt signaling molecule levels within each group are considered to be significant in this study. In order to detect the rate of change between baseline and 12-week intervention in both groups, and obtain a type 1 error rate of 5% and a power of 90%, a sample size of 17 subjects per study arm are needed. To account for an expected dropout rate of ~30%, we decided to increase this number to a group size of 25. Thus, a total of 50 breast cancer survivors will be included in the study. The minimum number of subjects for adequate study power was calculated with a sample size calculator.
                                                                                                                                                                                                                                                                                                                                                                                                                                                                                                                                  |
| Statistical analysis                 | 
Feasibility measures (acceptability, adherence, and adverse events etc.) are reported as numbers and percentages. Reasons for declining participation are analyzed descriptively with numbers and percentages of subjects declining for various reasons. Descriptive statistics are calculated to identify the means and standard deviations (SD) or standard errors of the mean (SEM). After Shapiro-Wilk normality test and variances analysis, parametric paired t-test or non-parametric Wilcoxon signed-rank test are used to compare the levels of health-related fitness, body composition, and serum biomarkers between before and after training, as appropriate. Pearson's and partial correlations are calculated to assess the relationships between serum levels of Wnt signaling molecules and other clinical parameters. All data are analyzed using SPSS 22.0 software (SPSS, Inc., Chicago, IL, USA). All statistical tests are two-sided and P-values less than 0.05 are considered significant.
                                                                                                                                                    |

[figure not shown]

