## OBJECTIVES

We hypothesize that regular exercise could be an effective strategy to reduce expression of Wnt signaling molecules in breast cancer survivors. The primary aim of this study is to compare the changes in serum WISP-1 and  $\beta$ -catenin levels elicited by exercise intervention. As a preliminary observation to this, an age-matched comparison in those baseline levels between cancer survivors and healthy persons will be conducted. As secondary aims, we will assess the effects of the intervention on kinanthropometric (body composition and physical fitness) parameters and blood gluco-lipid metabolic profile and analyze their relationship with Wnt signaling indicators.

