## METHODOLOGY

### *Study design*

**Randomization** The Lifestyles Of Health And Sustainability for Breast Cancer Survivors (LOHAS-BCS) is a single-center, two-armed randomized controlled trial. Eligible participants are randomly assigned to either an exercise intervention group or a control group using sealed, computer generated random numbers with the allocation ratio of 1 to 1.

**Study procedures** Demographic characteristics are collected from personal interviews and self-reported surveys. Clinical characteristics are obtained from electrical medical records. Measurements are conducted at baseline and 12-week intervention, which include anthropometry, body composition, health-related fitness levels, and blood sample collection.

**Blinding** Four research staff members who are unaware of group assignment performed all outcome assessments. The statistician is unaware of treatment allocation until completion of the statistical analyses. Participants are not blind to their assignment but are unaware of main outcome measures, and are instructed to avoid mentioning anything regarding their study experience to the assessors.

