**Interventions**

**Exercise group** The exercise training program is designed following the American College of Sports Medicine cancer guidelines (exercise intensity, frequency, time, and type), and are performed at least three times per week for total 12 weeks, under the direct supervision of exercise physiologists. Exercise training is conducted with individual's ratings of perceived exertion intensities within 11–13 that are gradually and moderately increased at 4-week intervals until reaching a rating of 13–15. Each session begins with a warm-up consisting whole body stretching and flexibility exercises for shoulder muscles stiffness such as finger climbing, shoulder glides (inferior, anterior, and posterior), and pendulum exercises for 10 min. The exercise program incorporates step aerobics on 17-cm (6.7-inch) platforms for 20 min followed by the strength training using body weight consisting of shoulder press, black burn exercise, wall push-up, biceps curl-up, plank exercise, leg bridge, squat, and calf raise for 20 min. At the end of the session, subjects perform cool-down involving easy walking and stretching exercises for 10 min (Table 1). Subjects in the exercise group are encouraged to participate in a home-based exercise session at least 30 minutes once and more weekly for 12 weeks.

**Control group** Participants in the control group are instructed to maintain their routine physical activities and not to participate any new exercise programs during the 12-weeks study period. Afterwards, the subjects who complete both pre and post-test received an opportunity to participate in the same exercise program that the intervention group has performed.

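### The trial is randomised and sized for a comparison of two arms, but the only planned test of an intervention effect is a within-group before-after test

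*Protocol*

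**What the plan says.** - **Design.** The Study design section describes a "single-center, two-armed randomized controlled trial", with participants assigned "using sealed, computer generated random numbers with the allocation ratio of 1 to 1".
- **Control arm.** Under Interventions, controls are "instructed to maintain their routine physical activities and not to participate any new exercise programs during the 12-weeks study period". The same section refers to their pre- and post-tests, and Study design schedules measurements at baseline and 12 weeks.
- **Aim.** Objectives states: "The primary aim of this study is to compare the changes in serum WISP-1 and" β-catenin brought about by the exercise intervention.
- **Planned test.** Data analysis names a paired t-test, with this as the alternative: "non-parametric Wilcoxon signed-rank test are used to compare the levels of health-related fitness, body composition, and serum biomarkers between before and after training". The Statistical analysis row of the Study Protocol Summary repeats this: "parametric paired t-test or non-parametric Wilcoxon signed-rank test are used to compare the levels of health-related fitness" and the other outcomes.
- **Other planned inference.** "Pearson's and partial correlations are calculated to assess the relationships between serum levels of Wnt signaling molecules and other clinical parameters".
- **Sample size.** The text describes the 25% difference as a within-group one. The formula beneath it has a group #1 and a group #2, an n for each, and an allocation ratio of 1.

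**The concern.** A paired t-test and a Wilcoxon signed-rank test each ask whether the change within one set of people differs from zero. Neither uses the other arm. The protocol names no two-sample test, group-by-time term or ANCOVA, so the control arm takes no part in the inference about exercise.

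Two errors then become possible. First, anything that moves both arms over 12 weeks could be credited to exercise: recovery after chemotherapy, familiarity with the fitness tests, regression to the mean, or a difference between assay runs. Second, readers may set two within-group P-values side by side and take a significant result in exercise with a non-significant one in control as evidence of a difference. That pattern is not a test of a difference.

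At stake is whether the trial can answer its own primary question with the protection that randomisation was meant to give.

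**Working it through.** **1. Inputs from the protocol**
- Mean 2104 and SD 472 pg/mL, 25% difference, two-sided alpha 0.05, power 90%, about 30% dropout (Sample size).
- WISP-1 kit inter-assay CV below 12% (Outcome measures).

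**2. Inputs assumed, because the protocol gives neither**
- Correlation ρ between baseline and 12-week values: 0 to 0.8.
- Shift shared by both arms: 5%, 10% or 12% of 2104, that is 105, 210 or 252 pg/mL. The 12% borrows the assay limit only as a convenient size.

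**3. The plan's own figure**

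Δ = 0.25 × 2104 = 526 pg/mL.

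n per arm = (472² + 472²) × (1.96 + 1.28)² / 526² = 445,568 × 10.4976 / 276,676 = 16.9, so 17.

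With dropout: 17 / 0.70 = 24.3, so 25.

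Both figures reproduce. The formula is the normal approximation for two independent groups. A paired formula with ρ = 0 would give the same 16.9, because the variance of the change is then also 2 × 472². But a paired formula has no second group and no allocation ratio, and the protocol's has both. By the noncentral t, 17 per arm gives 88.3% power for the two-group comparison.

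**4. The paired test when exercise does nothing**

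SD of change = 472 × √(2(1 − ρ)): 668 at ρ = 0, 472 at ρ = 0.5, 299 at ρ = 0.8.

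Noncentrality = shift / (SD of change / √17), with 16 degrees of freedom. The chance that the exercise-arm paired t-test is significant with 17 completers is:

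| Shared shift | ρ = 0 | ρ = 0.5 | ρ = 0.8 |
|---|---|---|---|
| 5% | 9% | 14% | 28% |
| 10% | 23% | 41% | 78% |
| 12% | 31% | 54% | 91% |

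A between-arm test subtracts the shared shift and keeps its nominal 5%.

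**5. Reading two within-group P-values side by side**

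If each of two identical arms is significant with probability p, then exercise significant and control not occurs with probability p(1 − p). The maximum is 0.5 × 0.5 = 25%. With the 12% shift and ρ from 0 to 0.8 it lies between about 9% and 25%.

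**6. Does the planned size support a between-arm test?**

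ANCOVA residual SD ≈ 472 × √(1 − ρ²). For 526 pg/mL and 17 per arm, by the noncentral t:

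| ρ | ANCOVA power | Change-score power |
|---|---|---|
| 0 | 88% | 61% |
| 0.3 | 91% | 76% |
| 0.5 | 95% | 88% |
| 0.7 | 99% | 98% |

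These figures are on the raw pg/mL scale, as in the plan's own calculation.

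**The case against.** **Intent to compare arms.** The sizing formula and the stated aim both point to a between-arm comparison, and an analysis plan that is not shown may contain one. The intent is plain, and this part stands: a reader might infer that the arms were never meant to be compared, and the protocol does not support that. But the protocol is not silent on the test. It names one, in two places, and that test does not use the randomised control. The mismatch with the sizing formula has to be reconciled in the protocol itself.

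**Other inference is planned.** The correlations fall under the same two-sided 5% rule, so it would be wrong to say that the paired test is the only inferential test. It is the only planned test of an intervention effect. The age-matched comparison with healthy persons concerns baseline levels and is not the randomised contrast.

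**The shared shift is hypothetical.** A reader might take the kit's 12% limit as a forecast of drift. The protocol does not support that: an inter-assay CV limit describes random run-to-run scatter, not a directional shift. Sera are frozen until analysis, and nothing says that baseline and 12-week samples go into different runs. If paired samples share a plate, assay drift would be smaller.

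**Controls are measured too.** A shared change would tend to show in the control arm, which could warn a careful reader. That is fair. It is why the claim is that a shared change could be credited to exercise, not that it would be, and why the side-by-side pattern is capped at 25%.

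**ANCOVA is a preference.** Any valid between-arm test would cure the defect. ANCOVA is preferred for its power.

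**Conclusion.** The point holds, and the text should be changed before the outcomes are analysed. The named test cannot answer the question that the trial randomises for, and it does not match the contrast for which the trial is sized. That conclusion comes from the wording alone and needs no assumption about drift.

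The size of the possible error does rest on assumptions. With no exercise effect, 17 completers and correlations of 0 to 0.8, the false-positive rate of the exercise-arm paired t-test runs from 9% (5% shift, no correlation) to 91% (12% shift, correlation 0.8), against a nominal 5%. No single value in that range can be called the expected one, because the protocol gives neither the correlation nor any shift.

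**What to change.** - **Data analysis, and the Statistical analysis row of the summary.** Make the primary analysis of WISP-1 and β-catenin, and the analysis of the other outcomes, a comparison by randomised group: ANCOVA of the 12-week value on arm and baseline value, reporting the adjusted difference with its 95% CI. Keep within-group changes as description only.
- **Sample size, and the matching row of the summary.** Describe the 25% as a difference between the groups, so that the words match the formula.

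The cost is a paragraph of analysis text and a phrase in the sample-size text. Baseline and 12-week values are already scheduled in both arms, and 17 completers per arm (25 enrolled) can stay as planned.
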